### Follow-up of adverse events

During the study, all AEs and SAEs must be followed up during the study period until resolution or stabilization.

After the end of the study, or at patient's premature discontinuation: Only ongoing AEs or SAEs related to the study IMP, or to non-IMPs required by the study protocol, that are still not “resolved” must be followed-up until they are resolved (with or without sequelae), or until the condition is stabilized or until the Investigator no longer estimates it is clinically significant in a written justification.

If no follow-up information can be provided, the Investigator must:

- Provide a written justification and
- Document the outcome as “unknown” (except for cases where the outcome is known, such as death)

## Pregnancy

Pregnancy is an exclusion criterion.

Highly effective contraception should be applied for both male and female subjects throughout the study and for at least 30 days after last avelumab treatment administration if the risk of conception exists.

However, any occurrence of pregnancy during the study period should be documented by the Investigator on the “PREGNANCY FORM” and faxed or emailed to AUB/IRB-related site and Merck KGaA. If a pregnancy occurs during the study period, the patient should be withdrawn from the study as soon as pregnancy is known and intake of the IMP should be discontinued immediately.

The Investigator should:

- Collect the name and the contact of the physician/obstetrician following-up the patient’s pregnancy
- Complete the “PREGNANCY FORM” and/or the “PARENT-CHILD/FETUS AE FORM”
- And fax or email it to AUB/IRB-related site and Merck KGaA as soon as possible.

A template of the “PREGNANCY FORM” is provided in Appendix 20. 4 and a template of the “PARENT-CHILD/FETUS AE FORM” is provided in Appendix 20.5.

FAX OR EMAIL TRANSMISSION

The “PREGNANCY FORM” and/or the “PARENT-CHILD/FETUS AE FORM” should be sent to:

**[contact] (AUB) / [contact] (Merck KGaA)

Or

**Email:** [contact] / [contact]

Specifying:

PROTOCOL Number and/or Title

Merck assigned Study Number

SUBJECT Number

SITE Number/PI Name

SAE/ONSET DATE

The progression of the pregnancy will be followed up by the Principal Investigator in collaboration with the Investigator or the patient physician and/or obstetrician, and the health of both the mother and newborn will be documented.

## Regulatory safety requirements

The decision to notify SAEs to Competent Authorities (CA)/Ethics Committee is under the responsibility of the Principal Investigator.

The Principal Investigator will ensure that the Investigators, and all other appropriate persons, are informed in a timely manner of findings that could adversely affect the safety of patients.

The Principal Investigator will communicate additional safety information to the appropriate Health Authorities/Ethics Committee and all Investigators, as it becomes available.

Whenever local regulations request from the Investigator to directly notify local Authorities and/or Ethics Committee, the Investigator should provide the Principal Investigator or its representatives with evidence of such notification.

# PARAMETERS AND ASSESSMENT CRITERIA

## Assessment of efficacy

The primary efficacy endpoint is the proportion of patients who achieve a pathological complete response, defined as no viable tumor cells on the resected specimen.

The secondary efficacy endpoints are:

1. PFS at 3 years will be estimated with the Kaplan-Meier method and presented with the 95% CI.
2. Evaluation of response by obtaining TRG just after surgery (week 16 or 17 ± 3 days).

## Assessment of safety

Secondary safety endpoints are the frequency, severity, and attribution of adverse events related to avelumab in a neoadjuvant setting.

AEs and SAEs from all patients followed throughout the study will be recorded and reported, as described in Section 9.5, whether or not the AE was determined to be related to the administration of IMP.

Safety evaluation will include the monitoring of the following items:

- - 1. Clinical assessments

| **Clinical assessment** | **Time of assessment** |
| --- | --- |
| Routine monitoring of vital signs (heart rate, blood pressure, and body temperature) | At inclusion  Every 2 weeks± 3 days during chemotherapy  Every 3 months after surgery for 3 years |
| Weight |
| Physical examinations: total body examination (i.e., general appearance, skin, neck, including thyroid, eyes, ears, nose, throat, lungs, heart, abdomen, back, lymph nodes and extremities) and a clinical neurological examination |
| Pelvic MRI (rectal protocol) | At inclusion  Prior to surgery: pelvic MRI (rectal protocol), optional |
| CT or PET scan of the chest and the abdomen | At inclusion |

- - 1. Laboratory assessment:

| **Blood assessments** | **Time of assessment** |
| --- | --- |
| CBC, BUN, creatinine, electrolytes, SGPT, SGOT, GGT, alkaline phosphatase, bilirubin | Prior to study initiation  Start of chemotherapy  Then every two weeks ± 3 days  Then prior to surgery |
| Free T4 and TSH | At inclusion  At least every 8 weeks during treatment  At end of treatment or 30 days post-treatment safety follow-up |
| Virology | At inclusion |

- - 1. Urine or serum pregnancy test:
       - For women of childbearing potential and who are sexually active must be performed at baseline and least every month during treatment.
       - It should be negative when the patient is enrolled in the study.

Significant findings of any safety evaluation must be recorded either on the Relevant Medical History/Current Medical Conditions eCRF (if present before signing informed consent) or on the AEs eCRF (if newly occurring or worsening since signing informed consent).

## Exploratory endpoints

The exploratory endpoints are:

1. Evaluation of biomarkers CD4+, CD8+ and CD3+ T cell infiltration, and changes in PD-L1 expression. This endpoint aims to demonstrate proof of concept that short-course radiation therapy up-regulates PD-L1 expression and induces immune cell infiltration.
2. Serum markers of inflammation: neutrophil/lymphocyte ratio.
3. Quality of life assessed using FACT-C questionnaire (FACT-C, English version 4 of 16 November 2007 or Arabic version 4 of 03 September 2014).

# DATA MANAGEMENT

## eCRF completion

### Introduction

All of the information required to be reported to the Principal Investigator as per protocol will be entered in the eCRF for each study patient. The eCRF must be completed by the Investigator or any study center staff designated by the Investigator. The Investigator is responsible for ensuring that data recorded in the eCRF are complete, accurate and legible. The eCRF should be completed before review by the CRA.

### General instructions

- - - 1. ***Overview***

The CRFs are electronic. CRFs should be completed in English.

The patient-reported outcome (FACT-C) should be completed by the patient in Arabic, or in English if the patient does not understand Arabic. Once completed, the site staff will do the data entry in the eCRF.

All data in the eCRF must come from and be consistent with the source documents, i.e. patient’s file or medical records.

Any discrepancy between the data in the eCRF and those in the source documents should be corrected by the Investigator.

Abbreviations will be avoided since they are often ambiguous.

- - - 1. ***Header information***

Header information should include at least:

The protocol number,

The name/number of the visit,

The date of the visit,

Patient identification number: patient number is recorded with the center number provided by the CRA at the set-up visit. The patient number is a sequential number incremented with each patient included in the order of signature of informed consent.

- - - 1. ***Recording dates and time***

Dates will be recorded in the eCRF using two digits for the day and the month and four digits for the year.

Example: February 28, 2014 must be entered as 28/02/2014.

Time will be recorded using four digits according to the 24-hour clock.

Example: 3:25 pm must be entered as 15:25.

- - - 1. ***Recording of missing data***

The Investigator should make every effort to provide the information required. Use of the following codes should be kept to a minimum.

The Investigator or designated person should enter in the eCRF:

UK: If the requested item is unknown or not available

NA: If the requested item is not applicable

ND: If the requested item was not done

- - - 1. ***eCRF corrections***

Discrepancies may be identified by the data management system automatically at entry or after entry via rules defining acceptable data. They can also by manually identified at any point during the review process by CRAs or Data Manager. Identified discrepancies will be shown as queries on eCRF and will need to be resolved by the Investigator or designated person.

All corrections to an original eCRF entry must indicate the reason for change. The Investigator is required to sign the eCRF after all data have been captured for each patient. If corrections are made after review and signature by the Investigator, he or she must be made aware of the changes, and his or her awareness documented by re-signing the eCRF.

- - - 1. ***Confidentiality***

Patient names must be kept confidential and should not appear on any eCRF page or study-specific documents provided to the CRO. The CRAs or other agents of the sponsor shall not access the site’s medical records unaccompanied by the site’s medical staff. Also, no personal health information is recorded by the CRA except as authorized by the IRB approved protocol; the IRB approved signed subject consent form and the signed clinical trial agreement.

- - - 1. ***eCRF Completion in case of premature withdrawal***

An eCRF must be completed for all patients with a signed informed consent up. Premature withdrawal must be documented on the end of study form of the eCRF with the cause having led to premature withdrawal.

### Specific Case Report Form instructions

Specific instructions for completing the eCRF will be detailed in a specific document “eCRF completion guidelines”.

## CRF and data handling

Data processing, from data collection to database lock, will be carried out in accordance with GCP (see ICH-E6, Section 5).

The database structure, data entry manual, coding rules and computerized validation, are defined in a Data Management Plan.

The database and data entry screens will be created in software specifically designed for clinical data management in compliance with ICH-E6 requirements.

All eCRF received in the Data Management Unit will be tracked by the Data Manager. The consistency of data will be checked by computerized programs and related queries will be generated for resolution by the Investigator. The database will then be updated accordingly.

Coding of medical terms and drug names, quality controls to ensure the overall quality and consistency of the database and reconciliation of SAE reports with the pharmacovigilance database will also be carried out.

At the end of the data handling process, a data review meeting will be held to prepare the database lock. After database lock, data will be transferred into a statistical software for the production of statistical analyses.

# STATISTICS

## Statistical analysis plan

The detailed technical aspects of the statistical analyses will be provided in the SAP. The SAP will possibly take protocol amendments into account and adapt to unexpected issues raised by the trial running and/or data that affect planned analyses in the protocol.

Any deviations from the protocol regarding the description of statistical analysis in the SAP will be discussed in the study report.

Prior to locking the database, a data review meeting will be planned to review individual data and validate the SAP.

The distribution of parameters, including safety data, will be summarized using descriptive statistics according to the study variable:

- Categorical variables (binary, nominal and ordinal) will be presented by contingency tables (frequencies and percentages). Number and percentages of missing data will also be mentioned.
- Quantitative variables will be presented by their mean, standard deviation, standard error, median, quartiles and range, minimum and maximum values. The number of documented values will also be mentioned.

The primary endpoint will be presented by number and proportion of patients who achieved pCR along with the one-sided 95% confidence interval. Using Kaplan-Meier method, the median PFS will be estimated along with its 95% confidence interval. Exploratory variables will be analyzed according to their scale of measurement by using mean ± standard deviation or frequency distribution for numeric and categorical variables respectively.

Frequency distribution for AEs and SAEs will be presented per cycle and per patient. Similarly this will be done for the SAE of grade 3 or above combined.

No subgroup analysis is planned.

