# DURATION AND DATES OF THE STUDY

The duration of this study depends on the results of the interim analysis, i.e., the probability of early termination, if only 2 or fewer patients achieve pCR at stage one (65.37% based on the study design). Interim analysis will be done on 13 patients once the surgery on the 13th patient is completed. The remaining patients will be enrolled based on the result of that analysis. The study duration is expected to be 4.5 years if the 2 stages of the study will be done. The first patient’s first visit is expected on 20 July 2018, and last patient last visit in on 02 May 2023. The 4.5-year duration includes 18 months of enrolment and 3 years of follow-up.

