## Sample size determination

Assuming the historical rate of pCR with short radiation followed by systemic 5FU-oxaliplatin chemotherapy is 16% to 19% (Bujko et al., 2016a) and the rate of pCR with the addition of avelumab increases to 35%, Simon’s two-stage design (Simon R, 1989) will be used. The null hypothesis that the true response rate is ≤16% will be tested against a one-sided alternative. In the first stage, 13 patients eligible for the primary efficacy analysis will be accrued. If there are 2 or fewer patients with a pCR in these 13 patients (2 patients out of 13 constitutes 15%), the study will be stopped. Otherwise, 23 additional (eligible) patients will be accrued for a total of 36 patients eligible for the primary efficacy analysis. The null hypothesis will be rejected if at least 10 patients out of 36 have a pCR. This design yields a type 1 error rate of 0.05 and a power of 0.8 when the true pCR rate is 35%. The use of the Simon 2-stage design enables an interim analysis for both efficacy and safety to be performed following treatment of the first 13 (eligible) patients. In order to achieve the eligible 36 patients for the primary efficacy analysis, the study might have to recruit 15 to 20% more patients and this will increase the sample size to 44 patients. This increase in sample size will also benefit the analysis of the secondary outcomes for example by possibly increasing the precision with the estimation of the progression free survival outcome.

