## Efficacy analysis

### Primary efficacy variable(s)

- - 1. ***Description of the primary efficacy variable***

The primary endpoint is the proportion of patients who achieve a pathologic complete response, defined as no viable tumor cells on the resected specimen, in the MITT set.

The primary efficacy variable is a dichotomous variable (yes/no) that will be summarized using a proportion.

- - - 1. ***Hypothesis Test and Primary Analysis Model***

A Simon’s two-stage optimal design will be applied with the following hypothesis:

- H0: p (pCR) ≤0.16
- H1: p (pCR) ≥0.35

If 2 or less patients achieved pCR in the first stage with 13 MITT patients, the study will be stopped, otherwise another 23 MITT patients will be added to the study (stage 2) and the results of the 36 MITT patients will be analyzed at the end of the study. If overall 10 or more patients achieved pCR, then the null hypothesis will be rejected with a type I error of 0.05.

In addition, the one-sided 95% confidence interval (Wilson Score method) of the percentage of patients with pCR will be estimated for all patients in the MITT set and the PP set.

- - - 1. ***Multiple comparisons and interim analyses***

Interim analysis will be done upon recruitment of the first 13 MITT patients to assess the futility and efficacy of the study.

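### The reported pCR rate and one-sided Wilson limit are fixed-sample quantities in a two-stage design: a modest, fixable mismatch that leaves the go/no-go decision unchanged

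*Protocol*

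**What the plan says.** Section 12.1 fixes the presentation of the result: "The primary endpoint will be presented by number and proportion of patients who achieved pCR along with the one-sided 95% confidence interval". The synopsis repeats this. Section 12.8.1 names the method and applies it to the MITT and PP sets: "the one-sided 95% confidence interval (Wilson Score method) of the percentage of patients with pCR will be estimated".

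The same section describes a Simon optimal two-stage design: "If 2 or less patients achieved pCR in the first stage with 13 MITT patients, the study will be stopped". Section 12.2 adds the second stage, "23 additional (eligible) patients will be accrued for a total of 36 patients eligible for the primary efficacy analysis", and the final rule, "The null hypothesis will be rejected if at least 10 patients out of 36 have a pCR". The test is one-sided: "The null hypothesis that the true response rate is ≤16% will be tested against a one-sided alternative". Section 4 gives the chance of stopping early, "if only 2 or fewer patients achieve pCR at stage one (65.37% based on the study design".

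No section names an estimate or limit that takes the stage-1 rule into account. Section 12.1 leaves technical detail to the SAP, but the interval method is already chosen in the protocol, and a different choice in the SAP would have to be discussed in the study report.

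**The concern.** In this design the sample size depends on the stage-1 result. A proportion out of a fixed n, and a limit computed as if n had been fixed, therefore do not have the properties usually claimed for them. The raw proportion is biased, and the Wilson limit is not the inversion of the two-stage test that decides the trial.

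The estimated pCR rate is the trial's main output. Section 1.4.2 says the study should give a basis for planning later randomized studies, and Section 9.2.3 judges benefit against historical controls. In a single-arm trial the rate and its lower limit are what later planners carry forward, so it matters what the limit covers and in which direction the rate leans.

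**Working it through.** **Inputs.** From Sections 12.2 and 12.8.1: p0 = 0.16, p1 = 0.35, n1 = 13, stop at 2 or fewer, n2 = 23, n = 36, reject at 10 or more. One-sided 95%: z = 1.645.

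**The plan's own figures.**
- Early stopping at 16%: P(X1 ≤ 2) = 0.10366 + 0.25669 + 0.29336 = 0.6537, the stated 65.37%.
- Rejection probability, Σ over x ≥ 3 of P(X1 = x)·P(X2 ≥ 10 − x): 0.0433 at 16% and 0.8008 at 35%. The stated 0.05 (as a cap) and 0.80 hold.

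**Bias of the raw proportion.** The estimate is x/13 if stopped and s/36 otherwise. At a true 16%:
- Stopped part: (1 × 0.25669 + 2 × 0.29336)/13 = 0.84341/13 = 0.0649.
- Continued part: [(13 × 0.16 − 0.84341) + 0.34628 × 23 × 0.16]/36 = (1.23659 + 1.27431)/36 = 0.0697.
- Sum 0.1346, so the bias is −2.5 points.
- Given stage 2: 0.0697/0.3463 = 0.201, so the bias is +4.1 points.

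The same sums elsewhere:

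| True rate | Bias, all outcomes | Bias given stage 2 |
|---|---|---|
| 16% | −2.5 | +4.1 |
| 19% | −2.9 | +3.5 |
| 25% | −2.8 | +2.4 |
| 35% | −1.6 | +1.0 |

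The largest overall bias is −2.9 points, near 21%.

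**Lower limits.** Wilson: [p̂ + z²/2n − z√(p̂(1−p̂)/n + z²/4n²)]/(1 + z²/n). At 10/36: (0.2778 + 0.0376 − 0.1284)/1.0752 = 0.174. The stagewise limit is the p that solves P(X1 ≥ 3, S ≥ s) = 0.05. The UMVUE is ΣC(12, x−1)C(23, s−x) / ΣC(13, x)C(23, s−x) over x ≥ 3.

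| pCR of 36 | Raw | UMVUE | Wilson limit | Stagewise limit |
|---|---|---|---|---|
| 9 | 25.0% | 29.6% | 0.152 | 0.144 |
| 10 | 27.8% | 31.3% | 0.174 | 0.164 |
| 12 | 33.3% | 35.2% | 0.220 | 0.207 |
| 13 | 36.1% | 37.4% | 0.244 | 0.230 |
| 15 | 41.7% | 42.2% | 0.292 | 0.278 |

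Both limits exceed 0.16 at 10/36 and fall below it at 9/36, in line with the decision rule.

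**Exact coverage of the Wilson limit.**

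| True rate | Two-stage design | Fixed n = 36 |
|---|---|---|
| 16% | 0.957 | 0.948 |
| 17% | 0.939 | 0.927 |
| 19% | 0.941 | 0.934 |
| 25% | 0.955 | 0.954 |
| 35% | 0.954 | 0.954 |
| Minimum, 16% to 40% | 0.926 (near 29%) | 0.920 |

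The shortfall is present, and slightly larger, with no stopping rule at all. The stagewise limit covers with probability at least 0.950 throughout 16% to 40%.

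**The case against.** The strongest reply is that nothing stated here is false and no decision moves. The test of at least 10 of 36 already accounts for both stages, the Wilson interval is offered in addition to it, and at n = 36 the two agree. Reporting the number and proportion is ordinary description that any plan would need. All of that stands, and it keeps the point small.

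A reader might infer three stronger things, none of which is supported:

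- **That the stopping rule invalidates the Wilson limit.** Coverage does drop below 95% at several rates, but fixed-sample Wilson at n = 36 drops as far (0.920 against 0.926). The reason to prefer the stagewise limit is that it matches the test and holds its level. Neither limit holds 95% given that stage 2 is reached: at a true 16% both miss with probability 0.0433/0.3463 = 12.5%.
- **That the raw rate flatters the treatment.** On average it is low, not high. The upward bias appears only among trials that continue.
- **That the UMVUE should replace the raw proportion.** It is unbiased only over all outcomes, stopped trials included. A stopped trial gives the same value, x/13, either way. Given stage 2, its upward bias is larger than the raw one: +11.5 against +4.1 points at 16%, and +2.8 against +1.0 at 35%. Over the whole design its root mean squared error is larger below about 28% (9.6 against 7.8 points at 16%) and somewhat smaller above (9.8 against 10.4 at 35%). At 10/36 it would move the headline from 27.8% to 31.3%, the optimistic direction for planning. That is a trade-off, not a correction.

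**Conclusion.** The point holds as a minor one. The protocol attaches a fixed-sample rate and limit to a two-stage design. The raw rate is off by at most 2.9 points overall, in the conservative direction, and by +1.0 to +4.1 points given stage 2 for true rates of 35% down to 16%. The Wilson limit lies about 1 to 1.4 points above the limit that belongs to the test for 10 to 15 pCR. Its coverage ranges below the nominal 95%, down to 0.926, mainly for reasons unrelated to stopping. The go/no-go decision, type I error and power are unaffected.

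The figures assume exactly 13 and 36 evaluable MITT patients. The protocol enrols 44 and computes the interval for all MITT patients, so the attained stage-2 size may differ, and the figures would then shift.

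**What to change.** In Section 12.8.1, with matching words in Section 12.1 and the synopsis:

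1. Name the stagewise-ordering one-sided 95% lower limit as the limit that accompanies the two-stage test. Specify a version that allows the attained stage-2 size to differ from plan (for example of the Koyama-Chen type).
2. Keep the Wilson limit, labelled descriptive.
3. Keep the raw proportion as the reported rate. Show the UMVUE beside it as supplementary, with a note that it is unbiased only over all outcomes and lies above the raw value when stage 2 is reached.

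The cost is a few lines of text and code, with no change to sample size, decision rule or conduct. The price is a lower limit about 1 to 1.4 points less favourable for 10 or more pCR (0.164 instead of 0.174 at 10/36, 0.207 instead of 0.220 at 12/36), and some conservatism at some true rates.
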